| Implementation  To what extent was the intervention delivered as intended?  What are the facilitators and barriers to implementing the programme from a patient, provider and programmatic perspective?  What are the essential components and adaptations necessary to delivering an NCD service in this setting?  What are the start-up and incremental costs of delivering such a service? | Fidelity of programme delivery  (Process Indicators;  indicators in bold also reflect quality of medical care) | Extent to which clinical guideline delivered as intended:  Number / % of eligible patients with HTN with annual FPG performed during the reporting period  Number/ % of eligible patients with diabetes that have had an annual foot check/ eye check performed during the reporting period  Number / % of DM patients that have micro-albuminuria or urinary protein testing during the reporting period  Number / % of DM patients on ACE inhibitor (ACEi) with Creatinine testing during the reporting period  Number/ % asthmatics and COPD with control review (spirometry or clinical) during the reporting period  Number / % of active cohort attending a health education session at last clinical visit within reporting period  Number of MHPSS group sessions taking place monthly during reporting period  Number/ % of referred patients attending MHPSS individual counselling sessions  Number/ % of times when clinical action taken based on clinical or laboratory findings according to guideline (see Annexe 2d for detail) | Clinical audit  Participant observation  Routine health facility cohort data |
|  | Adaptations | NCD care adaptations to the local setting (e.g. cultural adaptations; dietary and exercise, smoking advice)  Programme adaptations related to humanitarian setting and role e.g. response to patients’ psychosocial needs and NCD-relevant mental health co-morbidities | Key informant interviews  Participant observation  Semi-structured interviews with 12 MSF/clinic staff and 16 patients |
|  | Cost | Staff time  Start-up and recurrent implementation costs (indirect, intermediate and final cost centres)  Average unit costs and unit costs stratified by morbidity) | Key informant interviews  2 Focus groups with  Medicine/supply/ staff costs  Staff time estimates |

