| “Effectiveness”/ Quality of Care  What are the trends in clinical outcomes and quality indicators of the programme?  What are the perceived benefits/unintended consequences from a patient and provider perspective? | Clinical Outcomes | No./% patients with hypertension that have a most recent BP <= 140/90 6 and 12 months post enrolment and trend from baseline  Number / % of patients with diabetes that have a most recent BP <= 140/90 6 and 12 months post enrolment and trend from baseline  Number / % of patients with diabetes with last HbA1c < 8.0 %/ 7.0 % 6 and 12 months post enrolment and trend from baseline  Number/% with a reduction of >= 0.5 mmol/L in cholesterol level from baseline 6 and 12 months from enrolment  Number/% of patients with asthma / COPD free from exacerbations/ admissions in the previous 6 months  Number / % of patients who report decreased/quitting smoking within reporting period  Number / % of patients who report increased levels of exercise from baseline during reporting period  Trend recommended referrals to another facility for acute complications/specialist care, as a proportion of active cohort | Routine facility cohort data  Costing data (for incremental costing analysis)  2 Focus group with patients  Semi-structured interviews with approximately 12 clinic staff and 16 patients |
|  | Quality Indicators | Proportion of recommended referrals to other services that are appropriate as per guideline  Number/ % of active patients with CVD prescribed a statin during reporting period  Number/ % of patients with CVD prescribed aspirin during reporting period  Number/ % of patients with CVD prescribed at least one anti-hypertensive during reporting period  Number/% of patients with COPD/asthma with inhaler technique check documented  Number/ % of times when appropriate clinical action taken based on clinical or laboratory findings according to guideline (see Annexe 2d for detail)  Trend in defaulters as a proportion of active cohort during reporting period  Description of cohort deaths (patient characteristics) | Clinical audit  Participant observation  Routine health facility cohort data |
|  | Perceived Effectiveness | Patient and providers perspectives on effectiveness of programme components (clinical review, medications, HE, HLO, MHPSS, HV) | Key informant interviews  2 Focus groups with patients  Semi-structured interviews with 12 MSF/clinic staff and 16 patients |

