### 3.4.2 Cohort study main outcome measures

The principal **clinical outcome measures** for patients in the cohort are:

DM: HbA1c < 7 or 8%; proportion of patients meeting individualised target at last visit within the reporting period and trend from baseline

Hypertension: BP < 140/90 mmHg: proportion of patients at target at last visit within the reporting period and trend from baseline

Cardiovascular disease: change in total cholesterol level from baseline

Asthma / COPD: Free from exacerbations / admissions in last six months

The principal **quality of care outcome measures** are the following:

Number/ % of active patients with CVD prescribed a statin during reporting period

Number/ % of patients with CVD prescribed aspirin during reporting period

Number/ % of patients with CVD prescribed at least one anti-hypertensive during reporting period

Number/% of patients with COPD/asthma with inhaler technique check documented

Number/ % of times when appropriate clinical action taken based on clinical or laboratory findings according to guideline (see Annexe 2e for detail)

Description of trends and patient characteristics in programme defaulters and deaths

Proportion of recommended referrals to other services that are appropriate as per guideline

Death is defined as confirmed death reported by family or community member. A defaulter is defined as a patient who has not attended any NCD clinic appointments within the last 90 days, is not known to have died or moved out of the area, and has not been successfully contacted by phone on two occasions by the clinic registrar. The definition was changed in October 2016 to reflect the newly extended appointment interval for stable patients to: two consecutive missed appointments; not known to have died, moved out of the area, or become immobile and ineligible for home care; and has not been successfully contacted by phone on two occasions by the clinic registrar.

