### 3.4.6 Clinical audit

A paper-based checklist (Annexe 2d) will be used by a trained clinical staff member(s) to evaluate a sample of two hundred patient files with ten per cent of the sample cross-checked by the medical supervisor. A randomly selected sample of files of patients enrolled in the programme for over 12 months will be used. In addition, 65 files (based on a precision of 10%) from amongst the patients with asthma will be randomly selected, since the active cohort contains fewer than 300 patients diagnosed with asthma. The data will be anonymised, entered by a trained data entry operator into a password-protected Excel software database, analysed using proportions measured with Pearson’s χ2 test and reported with 95% confidence intervals.

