## Annex 2e: Clinical audit sample checklist

|  | Condition | YES | NO | N/A |
| --- | --- | --- | --- | --- |
| 1.0 | Diabetes | | | |
| 1.1 | Micro-albuminuria or urinary protein tested in the last year (Target = 80%)  ? | Y | N | N/A |
| 1.2 | Correct action taken based on micro-albuminuria test result? (Target = 80%)  ? | Y | N | N/A |
| 1.3 | Baseline CVD risk score done on enrolment? | Y | N | N/A |
| 1.4 | Prescribed statin in accordance with guideline (if risk score > 20% or known CVD)? |  |  | N/A |
| 1.5 | On ACE inhibitor (ACEi) inhibitor for HTN if no contraindication (Target 80%)  ? | Y | N | N/A |
| 1.6 | Creatinine tested prior to ACEi initiation? (Target 80%) | Y | N | N/A |
| 1.7 | Annual foot check done? (Target 80%) | Y | N | N/A |
| 1.8 | Correct foot score calculated? (Target 80%) | Y | N | N/A |
| 1.9 | Correct action taken based on foot score? (Target 80%) | Y | N | N/A |
| 1.10 | Annual eye check done or referral made? (Target 80%) | Y | N | N/A |
| 2.0 | Hypertension | | | |
| 2.1 | Annual glucose check done if not known diabetic? (Target 80%) | Y | N | N/A |
| 2.2 | Correct action taken if above target (diagnose diabetes or perform second test as per guideline)? (Target 80%) | Y | N | N/A |
| 2.3 | Annual CVD risk score done? (Target 80%) | Y | N | N/A |
| 2.4 | Annual cholesterol checked if not prescribed a statin? (Target 80%) | Y | N | N/A |
| 3.0 | Asthma | | | |
| 3.1 | Annual control review done (Target = 80%) | Y | N | N/A |
| 3.2 | Action taken following control review as per guideline i.e. step down/up on medications as appropriate? (T 80%) | Y | N | N/A |
| 3.3 | Inhaler technique check documented? (Target 80%) | Y | N | N/A |
| 4.0 | Referral | | | |
| 4.1 | Referral to acute care/specialist service appropriate according to guideline? (T 80%) | Y | N | N/A |

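### The inhaler-technique measure is defined for COPD and asthma together, but the audit items and the 65-file oversample that would supply it name asthma only

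*Protocol*

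**What the plan says.** Protocol section 3.4.2 lists among its principal quality of care measures: "Number/% of patients with COPD/asthma with inhaler technique check documented". Table 2 repeats this under Quality Indicators and gives three sources for that row: clinical audit, participant observation and "Routine health facility cohort data". The fidelity part of Table 2 (Implementation) adds a second respiratory indicator for both diseases: "Number/ % asthmatics and COPD with control review (spirometry or clinical) during the reporting period". COPD is an inclusion diagnosis (section 3.4.1).

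The audit in section 3.4.6 is to "evaluate a sample of two hundred patient files with ten per cent of the sample cross-checked by the medical supervisor". On the frame it says: "A randomly selected sample of files of patients enrolled in the programme for over 12 months will be used". A further 65 files, sized to a precision of 10%, "from amongst the patients with asthma will be randomly selected". The reason given is that fewer than 300 active patients have asthma.

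The form is headed "Annex 2e: Clinical audit sample checklist". Its parts are diabetes, hypertension, asthma and referral. Items 3.1 (control review), 3.2 (action after review) and 3.3 ("Inhaler technique check documented? (Target 80" per cent) all stand under 3.0 Asthma. COPD is not named anywhere on it.

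**The concern.** Two indicators have a combined COPD and asthma denominator, while the form and the added sample that feed them name one of the two diseases. This is not detail that can be left to an analysis plan, because the protocol itself fixes the indicator, the checklist and the sampling list.

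A principal measure is at stake. An auditor who meets a COPD file has no item headed for it and no instruction on whether to use section 3.0. One auditor may score it and another may mark it not applicable. The result could be published as a COPD/asthma percentage whose denominator holds only asthma patients, or an undefined mixture.

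**Working it through.** **Step 1. Indicator against collection tool.**

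| | Diseases named |
|---|---|
| Inhaler check, section 3.4.2 and Table 2 | COPD and asthma |
| Control review, Table 2 (and Table 1) | Asthma and COPD |
| Annex 2e, items 3.1 to 3.3 | Asthma |
| Oversample of 65, section 3.4.6 | Asthma |
| Random 200, section 3.4.6 | Any diagnosis, enrolled over 12 months |

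**Step 2. Can the other sources in Table 2 fill the gap?**

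- Routine cohort data, inhaler check: section 1.1.6 describes the recorded items. It mentions vital signs, laboratory results, medications, diagnoses, referrals, exercise, smoking and stage of change, but not inhaler technique.
- Participant observation: section 3.7.3 describes watching working practices, education sessions and clinic flow. That cannot give a number and percentage of patients whose file documents a check.
- Control review is different. Table 1 already lists it for asthma and COPD as a programme indicator, and Table 2 gives routine data as a source, so its COPD part may come from there.

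**Step 3. Reproduce the 65.** The protocol states 10% precision, 95% intervals and fewer than 300 asthma patients. I assume p = 0.5, which it does not state.

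- Without finite population correction: n0 = 1.96² × 0.5 × 0.5 / 0.10² = 96.04.
- With correction: n = n0 / (1 + (n0 − 1)/N).
- N = 200: 96.04 / (1 + 95.04/200) = 96.04 / 1.4752 = 65.1. This matches the stated 65.

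So 65 is coherent for an asthma list of about 200.

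**Step 4. What a combined list would need.** The combined number is not given, so N is varied.

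- N = 250: 96.04 / (1 + 95.04/250) = 69.6, about 70 files.
- N = 299: 96.04 / (1 + 95.04/299) = 72.9, about 73 files.

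If 65 files are kept, the half-width is 1.96 × √[(0.25/65) × (N − 65)/(N − 1)]:

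- N = 200: 10.0 points
- N = 250: 10.5 points
- N = 299: 10.8 points

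**Step 5. Effect on an asthma-only estimate.** For illustration, assume 200 asthma and 50 COPD patients, with 70 files drawn at random from the 250. The expected asthma count is 70 × 200/250 = 56. The half-width is 1.96 × √[(0.25/56) × (200 − 56)/(200 − 1)] = 11.1 points, against 10.0 from 65 asthma files.

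**Step 6. COPD files in the random 200.** The COPD share is not given. At assumed shares of 1%, 2%, 5% and 10%, the expected counts are 2, 4, 10 and 20 files. They can therefore be present, but their number is not controlled.

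**The case against.** The strongest reply is that this is a wording mismatch with little consequence.

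- Annex 2e is called a sample checklist. It also has no cardiovascular section and no aspirin item, although aspirin in CVD is a principal measure, so the form was not meant to carry every measure alone.
- Table 2 names two further sources.
- Section 1.1.6 introduces several of its lists with the word include and is not exhaustive. Respiratory exacerbations are missing from it, yet Table 2 takes that outcome from routine cohort data.
- The 200 files are not restricted by diagnosis, and no scoring rule says that COPD files are to be marked not applicable.
- The protocol promises one combined proportion and no separate COPD estimate.

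Most of this stands, and it limits the point. A reader might infer that COPD cannot be reported at all, that the audit is the only source, or that the COPD count must be zero. The documents do not support any of these: COPD files can fall in the 200, the form may still be adapted, and an unlisted routine field is possible. A reader might also hold the imprecision of a COPD-only estimate against the plan, but no such estimate is planned.

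The reply does not remove the mismatch. The aspirin comparison fails because section 1.1.6 does record medications, while it shows no field for inhaler technique. Observation cannot supply a documented-check percentage. The only tool shown with an item for this measure is headed asthma.

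**Conclusion.** The point holds as an inconsistency between indicator and tool. For the inhaler check, no listed tool explicitly captures COPD patients, and no sampling step provides for them. If the form is followed as written, a principal measure labelled COPD/asthma could rest on asthma files alone. The control-review indicator shares the heading problem to a lesser degree, since routine data may cover COPD.

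The bias in the reported percentage cannot be sized, because neither the number of COPD patients nor their rate of documented checks is given. What can be sized is the sampling consequence of putting it right: about 70 files for a combined list of 250 and 73 for 299, against the planned 65. These figures assume p = 0.5 and a finite population correction, the combination under which the planned figure reproduces at a list of about 200.

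**What to change.** Before the audit starts:

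1. Retitle Annex 2e section 3.0 Asthma/COPD, and state that items 3.1 to 3.3 are scored for every file with either diagnosis, including those in the random 200.
2. In section 3.4.6, draw the respiratory oversample at random from the combined asthma and COPD list. State the list size and recompute the number of files from it. If 65 is kept, restate the precision (10.5 points at 250 patients, 10.8 at 299).
3. Claim no separate precision for COPD, since its share is unknown.

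Alternatively, limit the inhaler measure in section 3.4.2 and Table 2 to asthma, and state that COPD control review is taken from routine cohort data. This needs no extra files but drops COPD from a principal measure.

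The main option costs a form heading, a changed sampling list and, for lists up to 299 patients, up to about eight more files (73 − 65). The asthma-only estimate becomes slightly less precise, by about one point in the illustration above. Left until after the audit, the correction would mean pulling files again.

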## Annex 2f: Patient self-report medication adherence and beliefs questionnaire

| **Section 1** | |
| --- | --- |
| **1.1** | **Age (tick one):**  16-19 20-29 30-39 40-49 50-59  60-69 70-79 80-89 90-99 |
| **1.2** | **Gender (tick one):** Male Female |
| **1.3** | **Marital status (tick one):**  Single Married Widow(er) Divorced |
| **1.4** | **Household size (tick one box from (a) and one box from (b)) :**  (a) How many people aged 16 or older live with you currently, including non-relatives.  0 1-2 3-4 5-6 > 6 |
| **1.5** | (b) How many children under 16 years of age live with you currently, including non-relatives.  0 1-2 3-4 5-6 > 6 |
| **1.6** | **Highest education level reached (tick one):**  None Primary Secondary High School University |
| **1.7** | **Diagnosis (tick all that apply):**  Diabetes Asthma Chronic Lung Disease (other than asthma)  Thyroid Hypertension Ischaemic Heart Disease/ Angina  Peripheral Vascular Disease Stroke / Transient Ischaemic Attack  Other Please specify: _____________________________________________________________________  ________________________________________________________________________________________ |
| **1.8** | **Please indicate the number of REGULAR medications on your most recent prescription**  **from the MSF clinic** (include tablets or insulin only; exclude equipment e.g. glucose strips etc. )  0 1 2 3 4  6 7-10 11-15 16-20 > 20 |
| **1.9** | **Do you take medications that you get from other sources?** Yes No |
| **1.10** | **If Yes, (circle all that apply):**  Pharmacy Family/friends NGO clinic MOH clinic Private clinic |

| **Section 2**    [copyright material removed] | | | | | | |
| --- | --- | --- | --- | --- | --- | --- |
|  | | | | | | |
|  |  |  |  |  |  |  |
|  |  | | | | | |
| MARS_5VA RH2002  Medication Adherence Report Scale _5 ©R Horne University of Brighton, 1999. | | | | | | |

| **Section 3**  [copyright material removed] |
| --- |
| The Beliefs About Medicines Questionnaire – Specific (BMQ-S11-plural). © R Horne, University of Brighton, 1996. |

| **4.1** | TO BE ANSWERED BY MSF STAFF MEMBER  Questionnaire filled by (circle on option): | Patient 1  MSF Staff 2 |
| --- | --- | --- |

1. <http://journals.plos.org/plosone/article?id=10.1371/journal.pone.0065174> [↑](#footnote-ref-1)

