### 3.5.3 Adherence questionnaire eligibility criteria, recruitment and sampling

A randomly selected sample (e.g. through randomisation of patient numbers) of MSF patients aged eighteen years or older attending either MSF clinic over a two–week data collection period, will be approached to fill the 17-item questionnaire, in order to give a sample size of 300 (based on previous studies ^25^). Questionnaires are presented in Arabic and should take approximately fifteen minutes to complete. The Arabic-fluent data collector will administer the questionnaire to patients with limited literacy and this will be recorded on the questionnaire.

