### 3.5.6 Adherence questionnaire data analysis

The originators of these scales require that they are analysed and reported in accordance with their instructions in order to promote uniformity and facilitate comparison of findings across studies. Results will be analysed using basic descriptive statistics. Analysis will include proportions and means, presented with 95% confidence intervals (95%CI). Adherence rates will be compared using multiple linear regression to explore the effect of age, gender, civil status, education status, type and number of morbidities, number of medications and whether administered by self or by the data collector.

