## 4.6 Data management and protection

All paper data containing identifying information (e.g. signed consent forms) and those that do not contain identifying information (e.g. filled adherence questionnaires) will be held securely in locked filing cabinets at the MSF office in Irbid. Electronic data will be password protected, and held on password-protected computers with only identified team members given access to the data and password. The encoded cohort dataset will have the coding removed after final analysis for this evaluation is completed. All data (other than active service data) will be stored for ten years following completions of the project and will then be permanently deleted and destroyed. Responsibility for this rests with the principle investigator.

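### As the text reads, the medication-count question in Annex 2f (item 1.8) has no answer for exactly five medications, although that count is a stated predictor of adherence

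*Protocol*

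**What the plan says.** Annex 2f, item 1.8, is worded "Please indicate the number of REGULAR medications on your most recent prescription". It counts tablets and insulin and leaves out equipment. The options stand on two lines: 0, 1, 2, 3 and 4 on the first, and "6 7-10 11-15 16-20 > 20" on the second. As the text reads, item 1.8 has no free-text line (item 1.7 has one) and no instruction on what to do when no box fits.

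Section 3.5.6 plans a multiple linear regression of adherence whose explanatory variables include "type and number of morbidities, number of medications and whether administered by self or by the data collector". Section 3.5.3 recruits patients "in order to give a sample size of 300". Section 4.6 counts the completed forms among "those that do not contain identifying information (e.g. filled adherence questionnaires"), and section 3.5.5 says the data will be anonymised.

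**The concern.** A list of tick-box options should give every possible answer exactly one box. Here a patient on five medications has none. Depending on what that patient does, the count is recorded one too low, recorded one too high, or missing.

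The item supplies a named predictor, so the gap reaches an analysis the protocol commits to. It would also be hard to repair afterwards: with anonymised data and no identifier on the form, the true count cannot readily be looked up in the clinic file. The two ways of completing the form may handle the gap differently as well. A staff member filling it in for a patient with limited literacy can write five in the margin, while a patient filling it in alone may guess or skip, and mode of administration is another variable in the same model. Finally, section 3.5 says the tool may be reused in Irbid and more widely within MSF, so a gap left now could be carried forward.

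**Working it through.** The protocol states no figure on this point to reproduce. The check has three parts.

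**1. Coverage of the options.** The values covered are {0}, {1}, {2}, {3}, {4}, {6}, {7 to 10}, {11 to 15}, {16 to 20} and {above 20}. Every whole number from 0 upward falls in exactly one set, except 5, which falls in none. There is no overlap and no other gap. Adding {5}, or replacing {6} with {5, 6}, makes the list complete.

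**2. How many patients could be affected.** The only input from the documents is the planned sample of 300 (section 3.5.3). The share on exactly five medications is not given, so the distribution is an assumption: Poisson with mean m, for which P(X = 5) = e^(-m) × m^5 / 120.

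| Assumed mean m | P(X = 5) | × 300 |
| --- | --- | --- |
| 2 | 0.1353 × 32 / 120 = 0.036 | 11 |
| 3 | 0.0498 × 243 / 120 = 0.101 | 30 |
| 4 | 0.0183 × 1024 / 120 = 0.156 | 47 |
| 5 | 0.00674 × 3125 / 120 = 0.175 | 53 |
| 6 | 0.00248 × 7776 / 120 = 0.161 | 48 |

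The range is 11 to 53 respondents. The share peaks at a mean of exactly 5, so the upper figure is the largest that a Poisson assumption can give.

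**3. How much a wrong tick matters.** Suppose every patient on five ticks 4 or 6. Each error is one unit, so the mean squared recording error is P(X = 5) × 1². A Poisson variable has variance m. The ratio of the two is 0.036/2 = 1.8%, 0.101/3 = 3.4%, 0.156/4 = 3.9%, 0.175/5 = 3.5% and 0.161/6 = 2.7% for means 2 to 6. The recording error is therefore at most about 4% of the spread of the predictor. This ignores the coarsening from the bands above 6, which is a separate matter.

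**The case against.** The strongest objection is that the gap may not be on the real form. It falls exactly at the line break between 4 and 6, and the tick-box symbols are absent from the text. If the printed label were 5-6 and its first part had been lost, five options per line would still be seen, so the even layout proves nothing. The same form uses a 5-6 band twice, in items 1.4 and 1.5. This objection stands in part: a conversion fault cannot be excluded. Against it, the form's other numeric lists came through without gaps, for example the age bands starting "16-19 20-29 30-39 40-49 50-59" and both household-size lists. The text, followed as it stands, leaves five without an answer.

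A second objection concerns harm. A reader might infer that about 50 patients are misrecorded in the part of the range where the predictor carries most information. The documents do not support that:

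- The figure of 47 to 53 needs an assumed mean of 4 to 6. Single-condition patients are eligible, and as worded the item leaves out inhalers, so a mean of 2 to 3 is no less defensible and gives 11 to 30.
- If five is mid-range, it has little leverage on a linear slope. With means of 4, 5 and 6, the squared distance of five from the mean is 1, 0 and 1, against average squared distances of 4, 5 and 6. If the mean is 2 or 3, five lies further out (9 against 2, and 4 against 3), but fewer patients are affected.

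A reader might also infer that patients who leave the item blank drop out of the regression, or that the unequal bands from 7 upward will be forced into a straight-line term. Section 3.5.6 states neither a complete-case rule nor how the variable is coded; banded counts can be entered as categories, and such details are commonly left to an analysis plan.

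It is also fair to say that section 3.5 calls this a small exploratory study, one aim of which is to test how the questionnaire performs.

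**Conclusion.** The point holds in a limited form. As the text reads, item 1.8 offers no answer for exactly five medications, and the item supplies a predictor named in section 3.5.6. Patients on five would be recorded one off or left missing.

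The number affected is not knowable from the documents. Assumed Poisson means of 2 to 6 give about 4% to 18%, or 11 to 53 of 300. If all of them ticked a neighbouring box, the bias in an exploratory regression would be modest; blanks would instead cost some precision, depending on a missing-data rule that the protocol does not give. No numerical result in the protocol changes. The conclusion is conditional on the original form showing the same gap, which needs to be checked.

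**What to change.** Check item 1.8 on the original form and on the Arabic version that patients will receive. If five is absent there too, add a box for 5, or change 6 to 5-6, before printing; either makes the list complete. A separate box for 5 keeps five and six apart and is slightly more informative. Asking for the exact number in writing is an optional alternative that would also remove the bands, but it is not needed to close the gap.

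The cost is one line on the form. Sample size, recruitment and the planned analysis are unaffected.
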